### 2.3. Design

The current study will employ a 24-week 2 × 2 crossover design. Participants will complete two 8-week dietary interventions, separated by an 8-week washout period. Participants will be allocated to a starting diet group, either the Mediterranean diet or the low-fat diet, using block randomisation and stratification based on age and gender. In Phase 1, participants will follow their starting diet for 8 weeks. All participants will then return to their habitual diet for 8 weeks, after which they will “cross-over” and complete the second 8-week intervention for Phase 2 (see Figure 1). All participants will therefore complete each experimental condition. 

The crossover design has been chosen for time and resource efficiency. As participants will act as their own control, potential differences between subjects in both observed and unobserved confounders that may be present in a medium-sized parallel-group design will be removed. This will reduce the potential for bias in estimating the treatment effect. In addition, repeat measures on the same individual allows for separate estimation of the true underlying value for each individual, the treatment effect and the measurement error. Separating the treatment effect from the measurement error will allow a more precise estimation of the treatment effect and fewer participants will therefore be required to detect any between-group differences. The reduced bias due to the removal of potential confounding variables will also enhance the internal validity of the design. An 8-week intervention period is expected to be adequate as similarly timed RCTs have demonstrated significant effects of nutrients contained in the Mediterranean diet, such as flavanols and omega-3s, on cardiovascular outcomes [46,48,121]. Further, the observed changes in cardiovascular outcomes were found to mediate improvements in cognitive function. As there is the potential for latency effects beyond 8 weeks, Potential carry-over effects will be assessed by testing for treatment × phase interactions, and it is anticipated that 8 weeks will be an adequate washout period to prevent cross-contamination between intervention phases [109]. Practice effects of cognitive tasks will be mitigated through the use of measures with strong test-retest reliabilities, counterbalancing of test order and the use of multi-level analysis that will allow the separation of measurement error (i.e., within-subject variability) from treatment effects.

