### 2.7. Power Calculation and Statistical Analyses

In order to detect a clinically relevant difference of 2.5 mm Hg in the primary outcome measure of systolic home blood pressure with at least 90% power, a sample size of 31 volunteers is required. A reduction of 2.5 mm Hg in blood pressure translates to a risk reduction at a population level in stroke, hypertension and CVD of between 7% and 15% [133]. This calculation assumes a within-group standard deviation (SD) of 14 mmHg, a within-subject correlation between the 4 blood pressure measures at each visit of *r* = 0.6 based on previous studies [135,136], and a between-phase within-subject correlation of *ρ* = 0.5. This correlation (*ρ*) and the cross-over design reduces the number of required participants by a factor of (1 − *ρ*)/2 = 4 [153] i.e., from approximately *n* = 124 for a parallel group design using ANCOVA (*n* = 62 per group) to *n* = 31 subjects in total. To account for a withdrawal rate of 30%, an additional 9 volunteers will be recruited. 

To detect a statistically significant difference in *Z* scores for the cognitive outcomes Total Cognitive Functioning, Memory, Processing Speed and Executive Functioning, a sample size of *n* = 22 is required. This calculation assumes power equal to 0.8, an α level of 0.05, a correlation between measurements of 0.6, and a moderate effect size (Cohen’s *d* = 0.5) signifying a treatment effect of 0.5 SD [137]. A moderate effect size has been chosen on the basis of similar nutritional intervention studies that have detected significant improvements in cognitive outcomes, which may indicate restoration of cognitive function and reversal of cognitive decline [46,152].

Independent *t*-tests and chi-squared tests will be used to compare baseline demographic, cardiometabolic, cognitive, well-being and dietary characteristics between those who completed the study and those who withdrew.

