To analyse the difference between dietary interventions a linear mixed-effects analysis will be performed to measure both within and between subject effects for cardiometabolic and cognitive outcomes. Potential confounding variables including weight loss, changes to physical activity, medications or dietary supplements, carryover and period effects will be included in the analysis. Potential carryover effects and treatment-period effects will be assessed by adding treatment × phase and treatment × order interaction terms in the mixed effects analyses. We will also assess possible seasonal effects by including a term for treatment × season interaction in a secondary analysis with season coded as a binary variable for Autumn or Spring versus Winter or Summer. Diet × period × energy intake interaction terms will be used to determine whether there are any significant changes in diet (total energy intake, macronutrient intakea, micronutrient intakes including sodium, and fatty acid ratios) between the two diet phases. If a significant change is detected in cognitive function a hierarchical regression will be performed to determine the influence of cardiometabolic outcomes. All statistical analyses will be conducted using SPSS for Windows, version 21.0 (SPSS Inc., Chicago, IL, USA) and Stata (version 14.2, StataCorp, College Station, TX, USA). Data will be presented as means ± standard deviation (SD) for descriptive statistics and as means ± standard error (SEM) for reporting estimated effects. All tests will be 2-tailed and *p*-values < 0.05 will be deemed statistically significant.

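### The cognitive sample size of 22 does not follow from its listed assumptions under the protocol's two-tailed rule: a paired crossover comparison needs 28, and 22 gives about 71% power

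*Protocol article*

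**What the plan says.** All the relevant statements are in the protocol article.

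- Section 2.3 fixes the design: "The current study will employ a 24-week 2 × 2 crossover design". Every participant receives both diets.
- Section 2.7 gives the cognitive requirement for Total Cognitive Functioning, Memory, Processing Speed and Executive Functioning: "a sample size of *n* = 22 is required".
- It then gives the inputs: "This calculation assumes power equal to 0.8, an α level of 0.05, a correlation between measurements of 0.6, and a moderate effect size". The effect size is Cohen's d = 0.5, glossed as "signifying a treatment effect of 0.5 SD". One correlation is listed. The sentence names no formula and does not say whether α is one- or two-sided.
- The end of section 2.7 settles sidedness for the analyses: "All tests will be 2-tailed and *p*-values < 0.05 will be deemed statistically significant".
- The blood-pressure calculation, earlier in section 2.7, requires 31 and adds 9 for 30% withdrawal, which makes 40. It starts from a parallel-group ANCOVA size and applies a crossover factor with a between-phase correlation of ρ = 0.5.

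**The concern.** The cognitive sentence prints a sample size together with its effect size, correlation, α and power. The design and the two-tailed rule supply the rest, so the number can be checked. It fails the check for a two-sided paired comparison and fits a one-sided one exactly.

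Cognition is part of the main objective in section 1.4, and section 2.7 makes a significant cognitive change the trigger for a further regression on cardiometabolic outcomes. A reader of section 2.7 would conclude that 22 completers give 80% power for each cognitive outcome. This is a disagreement between a published figure and its own stated assumptions, not a detail left to an analysis plan.

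**Working it through.** **Inputs (protocol article, sections 2.3 and 2.7).** d = 0.5 in units of the raw SD; correlation r = 0.6; α = 0.05; power 0.80; crossover, so the comparison is paired; tests two-tailed.

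**Step 1. Standardised paired difference.** With SD = 1, the variance of a within-person difference is 2(1 − r) = 2 × 0.4 = 0.8, so

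dz = d / √(2(1 − r)) = 0.5 / √0.8 = 0.559, and dz² = 0.25 / 0.8 = 0.3125.

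**Step 2. Normal approximation,** n = (z_α + z_power)² / dz².

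- Two-sided: (1.960 + 0.842)² / 0.3125 = 7.849 / 0.3125 = 25.1, so 26.
- One-sided: (1.645 + 0.842)² / 0.3125 = 19.8, so 20.

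**Step 3. Paired t-test** (noncentral t, n − 1 degrees of freedom, noncentrality dz√n).

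| n | Two-sided power | One-sided power |
|---|---|---|
| 21 | 68.3% | 79.6% |
| 22 | 70.6% | 81.4% |
| 27 | 79.8% | – |
| 28 | 81.4% | 89.2% |
| 31 | 85.3% | 91.9% |
| 40 | 93.2% | 96.6% |

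The smallest n reaching 80% is 22 one-sided, which is the printed figure, and 28 two-sided. Giving up one more degree of freedom for period (n − 2) changes neither requirement; two-sided power at 22 is then 70.4%.

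**Step 4. Other two-sided routes to 22.**

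- Parallel-group total × (1 − 0.6)/2: 126 × 0.2 = 25.2 (normal) or 128 × 0.2 = 25.6 (t).
- Repeated-measures F-test, correlation 0.6: 28 with two measurements, 23 with three, 19 with four. No three-measurement comparison is described.
- ANCOVA with 0.6 used as both the pre-post and the between-phase correlation: 16 to 19.
- ANCOVA with 0.6 as the pre-post correlation and ρ = 0.5 borrowed from the blood-pressure calculation: the variance is 2 × (1 − 0.6²) × (1 − 0.5) = 0.64, and n = 7.849 × 0.64 / 0.25 = 20.1, so 21 (normal). By t-test it is 23, with 79.8% power at 22.

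Only the last of these comes close to 22 for a comparison that the protocol describes, and it needs an input that the cognitive sentence does not list.

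**Step 5. Does using the baselines help on the single listed correlation?** Suppose all four assessments correlate at 0.6. The covariance between the difference in end-of-phase scores and the difference in baseline scores is 0.6 − 0.6 − 0.6 + 0.6 = 0. Adjusting for the baseline difference then leaves the variance at 0.8, and the two-sided requirement stays at 28.

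**The case against.** The strongest reply is that the protocol names no test for the cognitive calculation, so the paired t-test is the reader's choice. The preceding paragraph of section 2.7 sets out a different method for this trial: an ANCOVA size reduced four-fold for the crossover. Applied two-sided to the cognitive inputs, it gives 62.8 per group × (1 − 0.6²) = 40.2, so 41 per group and 82 in total. Then 82 / 4 = 20.5, which is 21, or 22 for two equal sequences. The planned mixed model would also use the baselines, which a two-value paired test ignores.

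Much of this stands. A reader might infer from the exact match that the sponsor ran a one-sided test. The documents do not establish that; they leave the method unidentified. But the ANCOVA route needs ρ = 0.5, which the protocol states for blood pressure only, and on the one correlation listed for cognition the baselines bring no gain (step 5). If that route was used, the cognitive sentence leaves out an assumption on which its result depends.

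It is also fair to say that the practical effect is small. Cognition is secondary, the trial was never planned to run with 22, and the primary outcome sets recruitment.

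**Conclusion.** The point holds as a misstated figure. On the assumptions listed for cognition and the two-tailed rule, 22 should be 28 (26 by normal approximation), and power at 22 is about 71% rather than 80%. This rests on reading d = 0.5 in raw SD units, as the protocol defines it, and 0.6 as the correlation between a participant's measurements under the two diets.

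Two further inferences should not be drawn.

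- **That the trial is underpowered for cognition.** With 40 × 0.7 = 28 completers, two-sided power is about 81%; with 31 it is about 85%.
- **That the protocol claims a safety margin between 22 and the planned completers.** It makes no such statement. The narrower fact is that 28 completers just meet the corrected requirement, since 27 would give 79.8%.

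Nor should the test-retest reliability of 0.54 in section 2.5.2 be put in place of 0.6. It belongs to a single reaction-time test, whereas the powered outcomes are composite Z scores.

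**What to change.** Do one of the following in section 2.7:

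1. Restate the cognitive requirement as 28 participants, two-sided, and note that 28 completers (40 recruits less 30%) give about 81% power for d = 0.5 at a correlation of 0.6.
2. If 22 came from a two-sided method with a further correlation, keep the figure, give the formula and that correlation, and say what each correlation refers to.

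In either case, state in the sample-size sentence that α is two-sided. The cost is one figure or one sentence; enrolment, design and analysis are unaffected.

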### 1.4. Objectives

The current study aims to evaluate the effect of a Mediterranean diet that meets Australian dairy and calcium recommendations. Specifically, a Mediterranean diet supplemented with additional dairy (milk, cheese and yoghurt) will be compared with a low-fat control diet on measures of cardiovascular risk and cognitive performance, quality of life and psychological well-being. A secondary aim of the current study is to determine the extent to which intervention effects on cognitive function are dependent on improvements to cardiovascular health.

For the primary prevention of CVD, targeting individuals at high risk may be more effective than targeting those at low or medium risk [101]. To evaluate the potential of a Mediterranean diet to reduce risk, the intervention will be administered to a sample with multiple risk factors of CVD, who are therefore at high risk of CVD and premature cognitive decline. As blood pressure a modifiable and strong predictor of CVD, brain atrophy and dementia, home blood pressure will be used as the primary outcome measure. Secondary outcomes will include measures of cardiometabolic health such as diastolic blood pressure, body mass index (BMI), waist-to-hip ratio, body composition, red blood cell fatty acids, blood lipids, Apolipoprotein E4 (ApoE4), C-reactive protein (CRP), blood glucose and insulin, estimated risk of dementia and measures of cognitive function. Specifically, memory, processing speed and executive function will be examined as each of these is sensitive to age-related decline, and task performance is predictive of cognitive ageing and risk of dementia and Alzheimer’s disease [30,102,103,104,105,106,107,108]. Further, these cognitive functions are negatively affected by hypertension, endothelial dysfunction, atherosclerosis and CVD [10,103,104,109,110,111,112,113,114,115,116,117,118,119].

The findings of this research will provide insight as to whether a Mediterranean diet that meets the dairy food group and calcium requirements of the target population is still capable of reducing risk of CVD and cognitive decline.

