### 2.4. Dietary Interventions

Weight loss has been linked to significant reductions in systolic and diastolic blood pressure, blood glucose, triglycerides and total cholesterol and inflammatory markers [122,123], as well as improvements to cognitive function [124], and so has the potential to mask the effects of a nuanced dietary intervention. To measure the effects of the intervention independent of weight loss, energy will not be restricted. Instead, participants will be instructed to consume all dietary interventions ad-libitum and self-regulate their food intake. If weight loss occurs the volunteer will be counselled to ensure that they are eating until satiated and that all dietary serving requirements are met. If weight loss continues changes in weight within each phase will be adjusted for statistically.

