#### 2.5.2. Secondary Outcomes

Secondary cardiovascular outcomes will include diastolic blood pressure and heart rate, body mass index (BMI), waist-to-hip ratio, body composition (percentage body fat, lean mass and abdominal adiposity) assessed using dual-energy x-ray absorptiometry (DEXA), fasting blood lipids, CRP, fasting plasma glucose, fasting serum insulin, erythrocyte cell fatty acids and Apolipoprotein E4 (APOEε4). A faecal sample will also be collected to explore the effects of a Mediterranean diet with adequate calcium on gut microbiota.

Fasting venous blood will be collected by venepuncture and centrifuged (4 °C, 4000 rpm, 10 min) before plasma and erythrocytes are separately aliquoted and frozen at −20 °C and then stored at −80 °C. Lipids, CRP, glucose and insulin will be measured at an external NATA accredited laboratory using standard procedures. Insulin resistance will be calculated using The Homeostasis Model Assessment (HOMA2) Calculator v2.2.3 (University of Oxford, Oxford, UK) [132]. This method to determine an insulin resistance score (HOMA2-IR) has been validated in samples with varying degrees of insulin sensitivity, with no differences shown between gender, age, BMI or diabetes status [133]. A higher HOMA2-IR score indicates greater insulin resistance. Participants with fasting insulin levels >57 mU/L, indicating diabetes related metabolic disturbance, will be excluded from these calculations. Erythrocyte fatty acids will be measured using direct transesterification as described by Tu et al. (2013) [134]. APOEε4, an indicator of increased risk for AD, will be determined using the TaqMan^®^ SNP Genotyping assay kit (Applied Biosystems, Warrington, UK) [135].

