### 2.6. Procedure 

Participants will attend two pre-baseline visits, four clinic assessment visits and six fortnightly visits at the Sansom Institute Clinical Trial Facility. 

Pre-baseline visits will take place one week before each dietary intervention begins. Participants will be provided with information about the study and asked to complete the SF-36, POMS, a six-day WFR and record home blood pressure for six days. The same measures will also be completed in the final week of each intervention at Weeks 7 and 23. 

Clinic assessment visits will take place at Weeks 0, 8, 16 and 24 (See Figure 1) and will include blood pressure measurement, anthropometry, DEXA scan and collection of fasted blood samples. Participants will be instructed to maintain their habitual levels of physical activity over the course of the trial. At each clinic assessment visit participants will be asked to provide details of habitual physical activity undertaken over the previous 2 months, including type of activity, frequency, duration and intensity. At Weeks 0 and 16 participants will be assigned their randomly allocated diet and will meet with the dietitian to discuss dietary guidelines. Participants will then consume a standardised continental breakfast before cognitive measures are administered. 

Fortnightly visits will be conducted throughout the intervention periods. At these visits weight will be measured and participants will have an opportunity to discuss their progress, challenges and goals with the dietician. 

The washout period will take place between the Week 8 and Week 16 clinic assessment visits, separating the two dietary intervention phases. 

Any changes to medications or dietary supplements will be noted throughout the course of the study and factored into the final analysis.

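### The one between-diet model described adjusts for changes that arise after diet allocation, so it does not give the total diet effect stated as the aim

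*Protocol article*

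**What the plan says.** Section 2.7 sets out the comparison of the diets in one place: "To analyse the difference between dietary interventions a linear mixed-effects analysis will be performed". It applies to the cardiometabolic and cognitive outcomes. The covariate rule follows. It names "Potential confounding variables including weight loss, changes to physical activity, medications or dietary supplements", and then carryover and period, as terms that will enter the analysis. The carryover and period terms in that sentence are ordinary crossover terms and are not at issue here.

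Three other sections bear on the same choice:

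- Section 1.4 gives the aim without qualification: "The current study aims to evaluate the effect of a Mediterranean diet that meets Australian dairy and calcium recommendations".
- Section 2.4 names a narrower target: "To measure the effects of the intervention independent of weight loss, energy will not be restricted". It then makes the adjustment depend on what happens in the trial: "If weight loss continues changes in weight within each phase will be adjusted for statistically".
- Section 2.6 adds: "Any changes to medications or dietary supplements will be noted throughout the course of the study and factored into the final analysis".

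The primary outcome is home systolic blood pressure (section 2.5.1). BMI and DEXA body composition are secondary outcomes (section 2.5.2), and section 1.4 counts both as cardiometabolic measures.

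**The concern.** A confounder of a randomised comparison would have to influence allocation. Weight loss, activity change, medication change and supplement change all occur after the diet is assigned, so none of them can. What they can do is lie between diet and outcome, or share causes with the outcome. Conditioning on such a variable changes the quantity estimated, and may bias it.

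At stake is what the main result means. A reader of section 1.4 expects the effect on blood pressure of being assigned the dairy-supplemented Mediterranean diet rather than the low-fat diet. A reader of section 2.4 expects that effect with any part through weight removed. Section 2.7 does not say which one the model estimates, and the rule for including weight differs between sections.

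**Working it through.** The plan gives no figure for this choice, so there is none to reproduce. The check compares the sections and then illustrates the size.

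**1. Timing.** Diet is assigned at Weeks 0 and 16 (section 2.6). The four covariates are changes observed after that.

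**2. Link to the outcome.** Section 2.4 states that weight loss is associated with reductions in systolic pressure. Intake is ad libitum under both diets, so weight may change. On the document's own account, weight is a possible path from diet to the primary outcome. The documents make no such statement for activity, medications or supplements.

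**3. Inclusion rule.** Section 2.4 adjusts for weight only if loss persists after counselling, with no threshold given. Section 2.7 adjusts in every case. Both cannot define the same model.

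**4. BMI.** Change in BMI equals change in weight divided by height squared, and adult height is effectively fixed. A model for BMI that conditions on weight change leaves almost no diet effect to estimate.

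**5. Size for systolic pressure.** Let D be the difference between diets in mean weight change (Mediterranean minus low-fat, kg), b the effect of weight on pressure (mmHg per kg), and β the within-diet slope of pressure on weight change. In a simple linear model:

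- total effect = direct effect + b × D
- adjusted coefficient = total effect − β × D

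The documents give neither b nor D. Assume a total effect of −2.5 mmHg (the magnitude targeted in section 2.7), D negative, and no common cause, so that β = b. The adjusted coefficient in mmHg is then:

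| b (mmHg/kg) | D = −0.5 kg | D = −1 kg | D = −2 kg |
|---|---|---|---|
| 0.5 | −2.25 | −2.0 | −1.5 |
| 1.0 | −2.0 | −1.5 | −0.5 |
| 1.5 | −1.75 | −1.0 | +0.5 |

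At 1 kg the shift is 0.5 to 1.5 mmHg, and 0.5/2.5 = 20% and 1.5/2.5 = 60% of the target.

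**6. Does adjustment give the weight-independent effect?** Suppose a common cause, per SD, adds 1 kg to weight change and 4 mmHg to pressure, and the remaining SD of weight change is 1.5 kg (all assumed). Then β = b + (1 × 4)/(1² + 1.5²) = b + 4/3.25 = b + 1.23. With D = −1 kg, a simulated 2×2 crossover (62 participants, 4,000 runs, residual SD of pressure 4 mmHg, means shown) gave:

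| Setting | True total | True direct | Unadjusted | Adjusted | Adjusted by formula |
|---|---|---|---|---|---|
| b = 1, no common cause | −2.5 | −1.5 | −2.49 | −1.50 | −2.5 + 1 = −1.5 |
| b = 1, common cause | −2.5 | −1.5 | −2.50 | −0.27 | −2.5 + 2.23 = −0.27 |
| b = 0, common cause | −2.5 | −2.5 | −2.51 | −1.26 | −2.5 + 1.23 = −1.27 |
| b = 0, no common cause | −2.5 | −2.5 | −2.49 | −2.49 | −2.5 |

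The unadjusted model recovers the total effect in every row. The adjusted model recovers the direct effect only in the rows without a common cause. A common cause acting with opposite signs on weight and pressure would push the adjusted estimate the other way.

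**The case against.** The strongest defence is section 2.4: a weight-independent effect is a declared target, so adjusting for weight is a deliberate choice. That stands as far as it goes. It does not settle the matter, because section 1.4 states the aim without that limit, and because covariate adjustment yields the weight-independent effect only under a condition the article does not discuss.

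Several stronger readings are tempting and are not supported:

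- *The diets change activity, medication or supplement use.* The article does not say so, and section 2.6 asks participants to keep activity habitual. A medication change could follow from a home pressure reading, since entrants take no antihypertensives (section 2.2.1), but that is inference.
- *Sodium, activity and adherence are unmeasured common causes.* All three are measured: sodium intake through the weighed food records (sections 2.5.2 and 2.7), activity at clinic visits (section 2.6), adherence by checklists and scores (section 2.5.2). The concern is with whatever common causes the model leaves uncontrolled.
- *No unadjusted result will be reported.* Section 2.7 labels no primary model, and this is a condensed article. Its silence does not show that none is planned.
- *Covariates will be chosen after seeing the blood pressure results.* The trigger in section 2.4 is continued weight loss, not blood pressure. What is shown is a conflict with section 2.7.

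The design also works against a large weight difference, through counselling when weight falls (section 2.4) and education when it rises (section 2.4.3).

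**Conclusion.** The point holds in limited form. As written, section 2.7 enters post-allocation changes into the only between-diet model described and calls them confounders. For weight, the article supplies the link to blood pressure itself, so the adjusted coefficient is not the total effect stated in section 1.4. It is the weight-independent effect of section 2.4 only if no uncontrolled common cause remains. For BMI and body composition, adjusting for weight change removes much of what is being tested. Sections 2.4 and 2.7 conflict on when weight is adjusted for.

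A reader might take 20% to 60% of the target as the expected distortion. It is an illustration resting wholly on an assumed slope of 0.5 to 1.5 mmHg per kg and an assumed 1 kg difference. The shift is nil if the diets do not differ in these changes and no common cause acts. What is established is an unclear target effect and an inconsistent adjustment rule, not a known bias of a given size.

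**What to change.** 1. State whether the primary effect is the total effect of the assigned diet or the weight-independent effect, and reconcile sections 1.4, 2.4 and 2.7 with that statement.
2. Make the primary model diet, period, sequence and participant. Pre-phase blood pressure may be a covariate, including the Week 15 measurement, which precedes the second diet; this fits the ANCOVA basis of the sample size in section 2.7. Include no covariate for a change that occurs during a diet phase.
3. Report models adjusted for weight, activity, medication and supplement changes as pre-specified supportive analyses of the weight-independent effect, stating the assumption of no uncontrolled common causes.
4. Do not adjust BMI or body-composition outcomes for weight change.
5. Remove continued weight loss as a trigger for adjusting the primary model.

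The cost is analysis wording only; no data collection or conduct changes. The downside is that the headline effect includes any part acting through weight. Readers who want that part removed will have the adjusted figure alongside.

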### 2.5. Outcomes

#### 2.5.1. Blood Pressure

Home measured systolic blood pressure will be the primary outcome. Home blood pressure assessments have stronger predictive power for complications of hypertension and mortality than clinic blood pressure assessments [127,128]. Further, multiple home blood pressure measurements have comparable reliability to ambulatory blood pressure measurements in evaluating hypertension [129]. Participants will be provided with an A&D Company Ltd. digital blood pressure monitor (model UA-767) and instructed to measure their blood pressure and heart rate every morning, afternoon and evening, for a period of six days at each of the four study time-points. Participants will be asked to take measurements at consistent times each day, at least one hour after the consumption of caffeine or alcohol and 30 min after food or exercise. Each measurement of blood pressure will follow a five-minute resting period in the seated position and three readings will be taken, spaced at least one minute apart [130,131]. Home blood pressure will be recorded at four time-points over the course of the trial, one week prior to clinic assessment visits (at pre-baseline, Week 7, Week 15 and Week 23). Blood pressure will also be measured in-clinic using an Omron Healthcare Co. digital blood pressure monitor (model 1A1B Hem-7000-CIL) at the beginning and end of each dietary phase. A similar protocol for in-clinic measurements will be used, with blood pressure and heart rate measurements following a five-minute resting period in the seated position. Three readings will be taken at each visit, spaced at least one minute apart.

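### In this 2 × 2 crossover the treatment × phase and treatment × order terms duplicate order and phase, so the carryover and treatment-period tests cannot isolate what they name, and the diet coefficient can become a single-phase comparison

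*Protocol article*

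**What the plan says.** Section 2.3 sets the design: "The current study will employ a 24-week 2 × 2 crossover design", and "Participants will complete two 8-week dietary interventions, separated by an 8-week washout period". It justifies the design by the within-person comparison ("As participants will act as their own control, potential differences between subjects in both observed and unobserved confounders") and gives the carryover method: "Potential carry-over effects will be assessed by testing for treatment × phase interactions".

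Section 2.7 plans a linear mixed-effects analysis of the diet difference. It lists potential confounders and says that "carryover and period effects will be included in the analysis". The next sentence says that carryover and treatment-period effects will be assessed by "adding treatment × phase and treatment × order interaction terms in the mixed effects analyses". The article does not give the full list of fixed effects, the coding, the contrast that will be reported as the diet effect, or what follows from a significant interaction.

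The sample size is set to "detect a clinically relevant difference of 2.5 mm Hg in the primary outcome measure of systolic home blood pressure with at least 90% power". It rests on a between-phase correlation of 0.5 and a reduction from 124 participants in a parallel-group design to 31 in the crossover. Section 2.5.1 adds that "Home blood pressure will be recorded at four time-points over the course of the trial": pre-baseline and Weeks 7, 15 and 23.

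**The concern.** A two-order, two-phase layout has four cell means and so supports four fixed-effect parameters. Intercept, diet, phase and order use all four. The two interactions in Section 2.7 must therefore repeat something already there, and a test labelled carryover or treatment-period may be a test of something else.

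The primary estimate is also affected. The trial is small because each participant is his or her own control. If a carryover term is carried in the model for the diet difference, the coefficient labelled diet can turn into a comparison of different people within one phase. That gives up the gain for which the crossover was chosen.

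**Working it through.** **Inputs.** From Sections 2.3 and 2.7: two orders, two phases, n = 31, between-phase correlation ρ = 0.5, SD 14 mmHg, target 2.5 mmHg, two-sided α = 0.05, power 90%. Assumed: equal order groups, compound symmetry, normal approximation. σ² is the variance of one end-of-phase value.

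**1. The plan's own reduction.** The diet effect has variance 4σ²/n in a parallel-group trial with n in total, and 2σ²(1 − ρ)/n in the crossover. The ratio is (1 − ρ)/2 = (1 − 0.5)/2 = 0.25, and 124 × 0.25 = 31. This step reproduces (the article prints the value as 4, which is its reciprocal). The step from SD 14 mmHg to 124 did not reproduce. The closest reading tried, ANCOVA with four pre and four post measures at r = 0.6 (effective SD 6.03 mmHg), gives 123 per arm rather than 124 in total. That is a separate matter. It means only that the 90% used below is the article's nominal figure.

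**2. Aliasing.** Code Mediterranean +1 and low-fat −1; Phase 1 −1 and Phase 2 +1; Mediterranean-first −1 and low-fat-first +1.

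| Cell | Diet | Phase | Order | Diet × phase | Diet × order |
|---|---|---|---|---|---|
| Med first, Phase 1 | +1 | −1 | −1 | −1 | −1 |
| Med first, Phase 2 | −1 | +1 | −1 | −1 | +1 |
| Low-fat first, Phase 1 | −1 | −1 | +1 | +1 | −1 |
| Low-fat first, Phase 2 | +1 | +1 | +1 | +1 | +1 |

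Diet × phase is identical to order, and diet × order is identical to phase. Intercept, diet, phase and order have rank 4. Adding both interactions gives six columns, still of rank 4.

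**3. Baselines kept as responses (eight cells).** If diet acts only at the end of each phase, treatment × phase can be fitted (rank rises from 6 to 7), but it is then an order × time contrast. Treatment × order still adds no rank.

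**4. Variance of the diet effect on end-of-phase values, n = 31, ρ = 0.5.**
- Diet + phase, with or without order: 2σ²(0.5)/31 = 0.0323σ².
- Reference-coded treatment × phase, or a first-order carryover term, raw diet coefficient: 4σ²/31 = 0.1290σ². This is the between-person variance in the reference phase (Phase 1 for a carryover term).
- The same treatment × phase fit, diet contrast averaged over phases: 0.0323σ².
- Sum-to-zero coding of treatment × phase: 0.0323σ².

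The ratio for the raw coefficient is 0.1290/0.0323 = 4.0, the exact reverse of the reduction in step 1. In general it is 2/(1 − ρ).

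**5. Power from a nominal 90%.** The standardised effect is 1.96 + 1.28 = 3.24. With four times the variance it is 3.24/2 = 1.62, and Φ(1.62 − 1.96) = 0.37. The same sum gives about 48% at ρ = 0.3 and 24% at ρ = 0.7.

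**6. With both phase baselines as responses.** Take a common ρ = 0.5 over the four time-points and equal baseline means in the two orders. The raw coefficient then has variance 0.0860σ². The ratio is 0.0860/0.0323 = 2.67, and Φ(3.24/√2.67 − 1.96) = 0.51. The averaged contrast stays at 0.0323σ².

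**7. Precision of the carryover term.** It compares participant totals between orders: variance (4/n) × 2σ²(1 + ρ) = 12σ²/31 = 0.387σ². At the effective SD of 6.03 the standard error is 3.75 mmHg, larger than the 2.5 mmHg that the trial is built to find.

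**The case against.** The strongest reply is that the article fixes less than a critic might assume. Much of it stands.

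- A reader might infer that the within-person comparison is lost under the plan. The documents do not support that. The loss needs a carryover or reference-coded interaction term in the model that gives the diet effect, and its raw coefficient reported. Section 2.7 fixes neither the coding nor the contrast, which an article may leave to the analysis plan. Its sentence on adding the interactions can also be read as a supplementary check on a base model.
- A reader might infer that the final model will be chosen on the carryover test, with a distorted error rate. No such rule is stated. Both sections say only that carryover will be assessed.
- A reader might infer that none of these terms can be fitted. Section 2.7 lists no order main effect, and diet + phase + treatment × phase is a full-rank model with four parameters. The redundancy arises when both interactions are used, or when either joins a model that already holds diet, phase and order.
- The treatment × phase (order) contrast is the conventional carryover test in this design, and the 8-week washout is the main protection.

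What does not fall away is the aliasing. The two terms are named methods, not details left out, and an analysis plan that follows the article inherits them. The convention behind the carryover test does not remove its confounding with order-group differences or a diet-by-period interaction. The treatment × order term has no meaning apart from phase. The statement that carryover will be included in the analysis keeps the single-phase coefficient a live possibility.

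**Conclusion.** The concern holds in a bounded form. On end-of-phase values, treatment × phase is order and treatment × order is phase. The treatment-period test is therefore the period effect, and the carryover test has three explanations that it cannot tell apart. This is algebra and depends on no numerical assumption.

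The effect on the primary estimate is conditional. In the worst case at ρ = 0.5 the variance is 4 times larger and a nominal 90% power becomes about 37%. With phase baselines as responses, the figures are 2.67 times and about 51%. With the diet contrast averaged over phases, or with order as a plain main effect, there is no loss. These figures take the article's 90% at face value. At the effective SD of 6.03 in step 1, the same change takes power from 64% to 21%.

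**What to change.** State the primary model as fixed effects for diet, phase and order with a random participant effect, without treatment × phase, treatment × order or carryover terms. Name the within-person diet contrast as the primary estimate.

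Report carryover separately, as the difference between orders in the change in home systolic blood pressure from pre-baseline to Week 15, with a confidence interval. State that it does not alter the primary model. Acknowledge that this check is also between-person, is open to chance imbalance and has low power. With ρ = 0.5 assumed between these two time-points, its standard error is σ√(2 × 0.5 × 4/31) = 0.36σ, or about 2.2 mmHg at SD 6.03.

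If phase baselines are used for adjustment, treat that as a sensitivity analysis, because the Week 15 value may itself carry residual Phase 1 effect.

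The cost is a few sentences in Sections 2.3 and 2.7. Both blood pressure values are already scheduled, so no new visits, measurements or participants are needed.
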